#### Randomization and blinding

After the baseline survey, 600 participating households’ main cooks will be randomly divided following a 1:1 ratio into the intervention group and the control group by the household demographic information, with 300 households in each group. The study coordinator will be responsible for the randomization and verification of the computer-generated intervention assignment with a randomization table. All the investigators, except for the study coordinator, will be blinded. The participants will be blinded and instructed not to inform the other participants of the treatment they receive.

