### Study sample

To calculate sample size, the following formula will be used:

$$ N=\frac{{\left({U}_{\alpha }+{U}_{\beta}\right)}^2\times 2P\left(1-P\right)}{{\left({P}_1-{P}_2\right)}^2} $$

where α = 0.05, β = 0.1, and then U_0.05_ = 1.96, U_0.1_ = 1.28. According to a previous study in China, the proportion of daily per capita salt consumption ≤6 g was 37.91% and the proportion increased to 45.91% after using salt-control spoons in participating households [16]. Thus, in this study, the increase in low salt consumption (≤6 g/d) with SALTCHECKER from about 38% (*P*_*1*_) to some 46% (*P*_*2*_), *P* = (*P*_1_ + *P*_2_)/2 = 0.42 was assumed. The sample size is calculated to be 799 cases. According to some similar salt-limiting trials, the dropout rate was 0.5–5% [18, 40–42]. And sampling error and invalid questionnaires may be 10–15%. Therefore, it was assumed 10–20% should be added on the basis of the estimated sample size, so 879–959 participants will be needed. The data of the tabulation on the 2010 population census of the People’s Republic of China (No. 1) indicated that the average household size in Chongqing is 2.70 (person/household) [43]. Therefore, 300 households’ main cooks in each of the intervention group and control group will be investigated in this study.

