### Analysis strategy

Statistical analyses will be conducted using SPSS version 22.0 (IBM Corp, Armonk, NY, USA). Descriptive statistics will be calculated for all the variables under examination. The counting data will be described by frequency and percentile, and the metrological data description will use mean, standard deviation and median. The demographic characteristics of the household members (e.g. age, gender, ethnicity, occupation, marital status, education level, height, weight and health status) will be analysed to examine the influencing factors of the household salt monitoring system by using multivariate regression analysis. Linear mixed models, generalized estimating equations (GEE) or t-test will be used to examine the predictors of added salt intake of each household member and salt consumption-related KAP of the household’s main cook and the moderators, mediators of the intervention effects. Correlation analysis will be used to test the link between the score of salt consumption-related KAP and daily added salt intake of each household member. Meanwhile, we will analyse the time trends of the daily added salt intake of each household member during the study period. The level of significance will be set at < 0.05. For the qualitative data analysis, the audio recordings will be transcribed verbatim by trained transcribers. Content analysis of the qualitative information gathered will be done using MAXqda. In addition, if there is enough data acquired about blood pressure, analysis of the impact of the system on blood pressure will be considered.

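### Allocation appears to be balanced on household demographics, but the permitted plain t-test cannot use those factors: conservative for KAP, probably too liberal for member-level salt intake

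*Protocol article*

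**What the plan says.** Under Randomization and blinding, allocation follows the baseline survey, and the households' main cooks "will be randomly divided following a 1:1 ratio into the intervention group and the control group by the household demographic information", 300 households per arm. The Procedure section confirms that the baseline survey collects household demographics. No stratification factor, block, pair or minimisation rule is named.

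The Analysis strategy states: "Linear mixed models, generalized estimating equations (GEE) or t-test will be used to examine the predictors of added salt intake of each household member". The same sentence covers the main cook's KAP and moderators and mediators of the effect. It does not say which of the three methods serves which outcome. Demographic characteristics have their own sentence, as possible influencing factors in a multivariate regression. They are not tied to the comparison between arms.

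The two primary outcomes have different units. Added salt is recorded for each household member, and KAP for one main cook per household. The development section derives each member's salt figure by sharing out a single household total.

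**The concern.** Simple randomisation would not need the demographic data, so allocating by them suggests that the arms are deliberately balanced on them. Balancing on prognostic factors removes their contribution from the chance difference between arms. A plain t-test still counts that contribution in its standard error, so with one value per household the interval is wider than it need be and the test runs below its nominal level. A null result on KAP would then be slightly more likely than the design requires.

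The same test has a different and probably larger fault on members' salt values. Several members of one randomised household would be counted as independent, which makes the standard error too small.

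**Working it through.** **The plan's own figure.** The Study sample section gives "where α = 0.05, β = 0.1", normal deviates 1.96 and 1.28, and proportions of 38% and 46% with mean 0.42. Its formula gives (1.96 + 1.28)² × 2 × 0.42 × 0.58 / 0.08² = 799.13, which matches "The sample size is calculated to be 799 cases". The formula is for independent persons. It contains no term for balancing and none for clustering.

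**Case A: one value per household (KAP, or household-level salt).**

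Let R² be the share of outcome variance explained by the allocation factors. The documents do not give it, so 0.05 to 0.20 is an assumption. Under balanced allocation:

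- true SE / t-test SE = s = √(1 − R²)
- true type I error of the t-test = 2 × [1 − Φ(1.96 / s)]

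Power depends on the effect, and the documents give none for KAP. Two assumptions bracket it:

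- *A1.* The adjusted test has 90% power. The t-test then has power Φ([3.2416 s − 1.96] / s), where 3.2416 = 1.96 + 1.2816.
- *A2.* The planned shift from 38% to 46% is put on a probit scale: Φ⁻¹(0.46) − Φ⁻¹(0.38) = 0.205 SD. With 300 households per arm, the standardised effect is 0.205 × √150 = 2.51. The t-test then has power Φ([2.51 − 1.96] / s) and the adjusted test Φ(2.51 / s − 1.96).

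| R² | t-test SE too wide by | True type I error | A1: t-test vs adjusted | A2: t-test vs adjusted |
|---|---|---|---|---|
| 0.05 | 2.6% | 4.4% | 89.1% vs 90% | 71.4% vs 73.1% |
| 0.10 | 5.4% | 3.9% | 88.0% vs 90% | 71.9% vs 75.4% |
| 0.20 | 11.8% | 2.8% | 85.3% vs 90% | 73.1% vs 80.2% |

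The power forgone is 0.9 to 4.7 points under A1 and 1.7 to 7.1 points under A2.

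A simulation of 600 households in six equal strata agrees. At R² = 0.20 the mean t-test SE was 0.0816 against a true 0.0733, with type I error 2.8%. At R² = 0.10 it was 0.0816 against 0.0785, with type I error 4.2%. With unrestricted allocation there was no distortion (5.2%).

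**Case B: members' salt values in a plain t-test.**

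The Study sample section gives "the average household size in Chongqing is 2.70 (person/household"), so take m = 2.7. Let ρ be the correlation within households and f the share of between-household variance explained by the allocation factors. Both are assumptions.

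(true SE / t-test SE)² = 1 + (m − 1)ρ − m f ρ

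With f = 0.2:

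- ρ = 0.3: 1 + 0.51 − 0.162 = 1.348; SE ratio 1.16; type I error about 9%
- ρ = 0.5: 1 + 0.85 − 0.27 = 1.58; SE ratio 1.26; type I error about 12%
- ρ = 0.7: 1 + 1.19 − 0.378 = 1.812; SE ratio 1.35; type I error about 15%

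The ratio falls below 1 only when f exceeds (m − 1)/m = 1.7/2.7 = 63%. In simulation with varying household sizes, ρ = 0.5 and f = 0.2, the t-test SE was 0.050 against a true 0.068, with type I error 15%.

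**The case against.** The premise rests on one ambiguous phrase. The article never says stratified or matched, and if allocation was unrestricted the t-test on KAP is valid. This stands, and it makes Case A conditional.

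The t-test is only one of three options, and the other two can include the allocation factors. The full protocol or an analysis plan may settle the choice. This stands in part: leaving details to another document is no fault. But the article positively lists a method that can use neither the apparent allocation factors nor the household structure, so it should not remain an option for the arm comparison.

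The size is uncertain. R² and an effect size for KAP are absent, and A2 borrows an effect on the proportion with low salt intake. This also stands, so the figures above are a range under stated assumptions.

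A reader might infer two stronger conclusions:

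- *That the t-test's intervals are too wide for both primary outcomes.* The documents do not support this. Salt intake is defined per member and derived from a shared household total, so a member-level t-test is likely to err in the other direction.
- *That planned power is being lost.* The sample size credits no gain from balancing. In A2 the t-test's own power rises slightly with R². What is forgone is extra precision that the design would make available.

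**Conclusion.** The point holds in a limited and conditional form. If households are balanced on prognostic demographics, a plain t-test on KAP or on household-level salt is mildly conservative. For assumed R² of 0.05 to 0.20, true type I error is about 4.4% to 2.8%, and roughly 1 to 7 points of power are forgone. If allocation was unrestricted, that test is not distorted.

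For member-level salt intake the t-test is probably anti-conservative: about 9% to 15% type I error for assumed ρ of 0.3 to 0.7 and f of 0.2. That fault does not depend on how the allocation phrase is read. On either count the plain t-test is a poor choice for the arm comparison.

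**What to change.** In the Analysis strategy, remove the t-test as an option for comparing arms. Estimate the arm effect on KAP and on added salt with the linear mixed model or GEE already named. Enter the demographic factors used for allocation as fixed covariates, or use a stratum or pair term if households are matched. For member-level salt intake, make household the cluster.

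In Randomization and blinding, name the factors and the method by which they enter the allocation. If allocation is in fact unrestricted, say so.

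The cost is wording. The demographic data are collected at baseline, and both models are already in the plan. A few degrees of freedom out of about 600 households are spent. For KAP the gain will be small if R² is small or if allocation was unrestricted.

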**Methods:**

A randomized controlled trial will be conducted among households to test the effect of a SALTCHECKER in Chongqing, China. The test modalities are the SALTCHECKER (with a smart salt checker and a salt-limiting WeChat mini programme) compared to a salt checker (with only a weighing function). The effectiveness of the system will be investigated by assessing the daily added salt intake of each household member and the salt consumption-related knowledge, attitude and practice (KAP) of the household’s main cook. Assessments will be performed at baseline and at 3 and 6 months.

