**Fig. 1 Fig1:**
[figure not shown]
System functional structure diagram

The front-end sensing system is also called the “smart salt checker”. It has a salt container and an electronic salt sensor. The electronic salt sensor is equivalent to a self-designed electronic weighing scale on the base of the salt container, which can weigh the salt in the container, with a weighing range of 0–250 g and a sensitivity of 0.2 g. After the user takes the salt each time, and the container is placed on the base with the lid closed, the processing unit of the electronic salt sensor can immediately detect and record the weight and the time of salt used.

The cloud analysis system can automatically calculate the individual added salt intake of each household member according to the information acquired from the terminal interaction system. The daily added salt intake of each household member will be calculated on the basis of the distribution of staple food consumption of residents in the household. Daily intake estimates of added salt for each household member (g/standard) = (30 days’ intake of added salt by the surveyed household × standard daily number of each member in the household/standard daily number of all people in the household)/30 [39].

The terminal interaction system is a salt-limiting WeChat mini programme; through the programme, basic data can be acquired of the participating household’s main cook and other household members, such as their age, gender, occupation, marital status, education level, height, weight, labour intensity, health status, the number of people per meal and meal ratio per day for members aged>2 years old in their household. Participants with hypertension will also be encouraged to provide data on blood pressure, and the time and tool of blood pressure measurement.

Overall, the SALTCHECKER contains three key features: (1) self-monitoring: to automatically calculate the daily added salt intake of each household member, (2) questionnaires: to investigate the basic demographic information of the household’s main cook and other household members and salt consumption-related KAP of the household’s main cook, (3) personalised reports: through salt-limiting WeChat mini programme, professional nutrition experts in our research group will provide the daily added salt intake of each household member and corresponding healthy salt-using suggestions for specific household members to the household’s main cook.

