### Recruitment

The households will be recruited from Chongqing, China. The study will be advertised in cooperative communities. The following strategies will be used sequentially until the desired sample size is achieved: (1) posters and project leaflets will be distributed; (2) advertisements will be circulated on social media, such as WeChat and Weibo platforms; (3) the project will be presented in the community by project manager or project members in the form of health seminars; and (4) the use, function and advantages of the SALTCHECKER will be demonstrated on-site.

Inclusion criteria: (1) the household’s main cook (involved mainly in household cooking); (2) plan to be living in Chongqing, China for at least 6 months; (3) own a mobile phone (iOS or Android) with Internet access; (4) and agree to have the WeChat mini programme on their mobile phones.

Exclusion criteria: (1) currently using a self-monitoring system or device to track or log living behaviour in household members; (2) having been involved in other salt experiments in household members; and (3) prior history of cognitive or verbal impairments or other diseases that may impact on study participation.

Interested household main cooks or their household members who are already using a self-monitoring system or tracking device will be excluded to avoid the potential confounding effect. The reason is that popular health apps or tracking device frequently implements various behavioural change strategies, which may affect participants’ behaviour.

On the basis of a computer-generated list in the statistical software IBM SPSS version 22.0 (IBM Corp, Armonk, NY, USA), we will randomly select 600 households’ main cooks (who meet the above-mentioned inclusion criteria) from the available household main cooks in the project database. Written informed consent will be collected from all the participants.

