#### Questionnaire survey

A self-administered questionnaire will be designed based on the local and international literature to assess the salt consumption-related KAP of the household’s main cook. The questionnaire will be sent to the household’s main cook through the salt-limiting WeChat mini programme. After the pre-investigation, the reliability and validity of the questionnaire will be tested. The questionnaire will include the following three parts:
Knowledge of salt consumption, such as the daily recommended intake of salt, high-salt diet hazards, recognition of seasonings and food with high sodium, etc. The knowledge of salt consumption is measured (0 = no, 1 = yes, 0 = do not know), and some items require reverse coding.The attitude of salt consumption, such as the attitude to salt-limiting or low-salt diets, awareness and intention of choosing a low-salt diet, etc. will be assessed using the 5-point Likert scale (1 = strongly disagree to 5 = strongly agree) questions.The practice of salt consumption, such as the use of low-sodium salt, proper use of salt-limiting spoons, selection of low-salt food, requiring low-salt food in restaurants, selection of food based on the nutrient list, etc. will be measured using the 5-point Likert scale (1 = strongly disagree to 5 = strongly agree) questions.

A total score will be calculated for the above items, and a high score will represent a high KAP.

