#### Control group

The household’s main cook in the control group will have access to the smart salt checker with only the weighing function.

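### The stated blinding cannot hold with these two arms, and the weighing-only control is not reconciled with data routes that run through the WeChat mini programme

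*Protocol article*

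**What the plan says.** On blinding, the Randomization and blinding section says of participants: "The participants will be blinded and instructed not to inform the other participants of the treatment they receive". Of staff it says: "All the investigators, except for the study coordinator, will be blinded".

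On the arms, the Intervention group section gives cooks a smart salt checker, monthly personalised reports and health education through the mini programme, and real-time access to nutrition experts for six months. Control cooks "will have access to the smart salt checker with only the weighing function". The abstract and the Procedure section draw the same contrast. The section on the development of SALTCHECKER says of the reports that "professional nutrition experts in our research group will provide the daily added salt intake of each household member".

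On measurement, the two primary outcomes are each member's daily added salt intake and the main cook's KAP, both at baseline, 3 and 6 months. The sensor in the container weighs household salt. The cloud system then works out each member's share "according to the information acquired from the terminal interaction system", and the development section identifies that system as the mini programme. The KAP questionnaire goes to the "main cook through the salt-limiting WeChat mini programme", and the Quality control section has it sent automatically to participants at all three times. Agreement to have the mini programme on the phone is an inclusion criterion for every cook. The Discussion, under limitations, says participants can look at their data there whenever they are online.

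**The concern.** Two properties of the design are stated in terms that its own description does not support.

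The first is blinding. A reader told that participants and nearly all investigators are blinded will discount reporting bias. KAP is a self-completed score, largely on Likert items, from the cook whom the intervention teaches low-salt norms. A cook who knows that he or she is being coached can move those answers without any change in behaviour.

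The second is the control condition. If it is a checker that only weighs, the protocol does not say how control households supply the meal and household data needed for member-level salt, or how they answer the KAP questionnaire. If they do have the mini programme, the protocol does not say which of its functions are switched off. Automatic calculation of each member's daily salt is listed as the self-monitoring feature of the SALTCHECKER, so controls who could see those values would receive part of what is being tested.

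**Working it through.** No figure in the protocol bears on this point, so the check sets the sections side by side.

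1. **Can participants be blinded?** The intervention arm receives reports, education and expert answers that the recipient sees. The control arm receives none of these, and the article describes no sham report or attention control. The sentence that declares blinding also tells participants not to disclose their treatment, which presumes that they know it. Blinding to treatment content is therefore not achievable. Something narrower, such as the study hypothesis, might be concealed, but the article does not say so.

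2. **Can all investigators except the coordinator be blinded?** The reports come from experts described as part of the research group, and experts also give the salt-limiting guidance. Anyone writing to a household under this scheme knows that it is an intervention household. If these experts count as investigators, the statement is wrong for them. Nothing shows that other investigators, outcome handlers or analysts are unblinded.

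3. **Which outcome data need the mini programme?**
   - Household salt weight: no. The sensor records it automatically for participating households.
   - Member-level salt, which is the primary outcome: yes, for the split. The formula multiplies 30 days of household salt by a member's standard daily number over that of the whole household, and divides by 30. The household and meal information (members' characteristics, people per meal, meal ratio) is acquired through the mini programme.
   - KAP, the other primary outcome: yes. It is sent through the mini programme.

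4. **Do controls have the mini programme?** The abstract, Procedure and Control group sections define the contrast as a checker with the programme against a checker that only weighs. The inclusion criteria and the Online questionnaire survey section make no distinction by arm. Randomization follows the baseline survey, whose questionnaire goes through the programme. The Procedure section also says that member-level intake is calculated using SALTCHECKER, which the abstract defines as including the programme.

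5. **What follows under each reading?**
   - Controls do not have it after randomization: member-level salt and follow-up KAP have no described route in 300 of the 600 households.
   - Controls have it: the data can be collected alike, but the control description is incomplete. The access to data described under limitations is not restricted by arm, so controls may get self-monitoring feedback. Such feedback, if it works, lowers control salt and pulls the estimated difference towards zero.

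Both readings leave the sections needing to be reconciled.

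**The case against.** The strongest reply is that the flaw is one of wording. Every eligible cook must agree to the mini programme, the questionnaire is sent to participants without distinction, and the baseline questionnaire runs through the programme before allocation. The weighing-only phrase may describe the device alone, and a restricted control version may already be intended. This stands to a large extent. A reader might infer that controls lack the programme, or that the arms are measured differently; the protocol establishes neither. Nor are both outcomes wholly collected through the programme, since salt weight comes from the sensor in both arms.

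Three other stronger readings also fail.

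- One might infer that recording completeness differs by arm because reminders sit in the programme. The sensor records without manual entry, and the free salt, monthly rewards and weekly text messages are not limited to one arm. A difference is possible but not shown.
- One might infer that all cooks see the full system before allocation, because "the use, function and advantages of the SALTCHECKER will be demonstrated on-site". This is the last of four recruitment strategies used in sequence until the target is met, so some or all cooks may never see it.
- One might infer that no investigator is blinded. The text supports doubt only about the experts who deliver the intervention.

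The reply does not rescue the blinding statement. No reading of the control arm hides from a cook whether reports and expert advice arrive. It also does not say which functions controls have.

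**Conclusion.** The point holds in two parts. First, participant blinding is claimed but cannot be achieved with these arms, and blinding of the report-delivering experts is doubtful. The main consequence is for KAP, where self-report by cooks who know their allocation can favour the intervention. Second, the weighing-only control description conflicts with the data routes for KAP and for the split of salt among members. It leaves open whether controls have no described route or may receive diluting feedback.

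Neither effect can be quantified from the protocol, and no figure is offered. The first part assumes that no sham content exists for controls, as none is described. The second rests on an ambiguity and not on a demonstrated difference in measurement. The doubt about the experts assumes that they count as investigators.

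A reader might go further and ask for KAP to lose its primary status, or for an error-rate adjustment across the two primary outcomes. Neither follows from this point. KAP is part of the stated aim, and multiplicity is a separate matter that an analysis plan not shown here may settle.

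**What to change.** Reconcile the abstract, the development of SALTCHECKER, Recruitment, Procedure, Questionnaire survey, Control group, Online questionnaire survey and limitations text by stating exactly which mini programme functions controls have. The cleanest choice is a data-collection-only version: household and meal data, the KAP questionnaire and the same recording reminders as the intervention arm, with no reports, education, expert chat or view of salt totals. Limit the statement that participants can view their data at any time accordingly.

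Replace the blinding statement. Describe the trial as open label for participants and for the experts who deliver the intervention, and name a data analyst who remains blinded to allocation. Report KAP explicitly as unblinded self-report.

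The cost is a restricted build of existing software, protocol wording and a less favourable description of the design. Both changes should be settled before households are randomized, because they determine what the trial compares and how control outcomes are obtained.
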